## Abstract

**Background:**

Families of children living with chronic illness are more vulnerable to mental health problems, however this can be ameliorated by a family’s resilience. The Child Illness and Resilience Program (CHiRP) will develop and evaluate a parent-focussed family intervention designed to increase the resilience and wellbeing of families living with childhood chronic illness.

**Methods/Design:**

The study will be conducted in an Australian regional paediatric hospital and will use a stepped care intervention that increases in intensity according to parental distress. All parents of children discharged from the hospital will receive a family resilience and wellbeing factsheet (Step 1). Parents of children attending selected outpatient clinics will receive a family resilience and wellbeing activity booklet (Step 2). Parents who receive the booklet and report psychological distress at three-month follow-up will be randomised to participate in a family resilience information support group or waitlist control (Step 3). The Step 3 control group will provide data to compare the relative effectiveness of the booklet intervention alone versus the booklet combined with the group intervention for distressed parents. These participants will then receive the information support group intervention. All parents in Step 2 and 3 will complete baseline, post-intervention and six month follow up assessments. The primary outcomes of the study will be changes in scores between baseline and follow-up assessments on measures of constructs of family resilience, including parental wellbeing, family functioning, family beliefs and perceived social support. Qualitative feedback regarding the utility and acceptability of the different intervention components will also be collected.

**Discussion:**

It is hypothesised that participation in the CHiRP intervention will be associated with positive changes in the key outcome measures. If effective, CHiRP will provide an opportunity for the health sector to deliver a standardised stepped care mental health promotion intervention to families living with childhood chronic illness.

**Trial registration:**

Australian clinical Trials Registry ACTRN 12613000844741

Universal Trial Number (UTN): 1111-1142-8829

## Background

Almost two in five families in Australia live with a child with a chronic illness (AIHW 2012). A chronic illness is one that is prolonged in duration, does not often resolve spontaneously and is rarely cured completely (Dowrick et al. 2005). It includes illnesses such as asthma, diabetes, cystic fibrosis, musculoskeletal and inflammatory disorders and gastroenterological disorders. Better survival rates mean the number of children living with chronic illnesses are increasing and consequently, there is a growing need to better understand the family impacts of caring for a child with a chronic illness (O'Brien et al. 2009; Scholten et al. 2011).

Children and young people who live with a chronic illness experience a range of persistent stressors that can increase their risk of developing mental health problems (Barlow & Ellard 2006; Cadman et al. 1987; Combs-Orme et al. 2002; Lavigne & Faier-Routman 1992; Mikkelsson & Sourander 1997; Sein 2001). For example, these children may need to manage symptoms that introduce physical and lifestyle limitations, including restricted participation in school and sport, as well as treatment effects and the impact of incorporating ongoing treatment into daily activities. These factors may limit spontaneity, create challenges for social relationships, and generate concerns about the future (Scholten et al. 2011; Gannoni & Shute 2010; Taylor et al. 2008).

The social and emotional impacts of living with childhood chronic illness are not confined to the child or young person themselves; they are shared with other family members (Barlow & Ellard 2006; Bauman et al. 1997; Raina et al. 2005). Parents of children and young people living with a chronic illness experience increased levels of stress due to intensified demands of their care and support role, financial pressures, and strains on their relationships with immediate and extended family members (Gannoni & Shute 2010; Raina et al. 2005; Barlow et al. 2006; Melnyk et al. 2001; Tong et al. 2008). Siblings are at increased risk of anxiety and intense emotions, experience confusion and difficulty communicating about the illness, may feel overlooked, and can experience negative changes to family and social functioning as a result of their sibling’s illness (O'Brien et al. 2009; Gannoni & Shute 2010; Bellin & Kovacs 2006; Besier et al. 2010; Strohm 2008).

While the experience of living with childhood chronic illness can increase vulnerability to mental ill-health, there is a growing body of research that suggests despite increased risk, some families are able to positively manage the impacts of the illness on their lives (Bellin & Kovacs 2006). Such families utilise their experience of managing the illness to develop stronger relationships, coping skills, refocus priorities, recognise opportunities and adapt to the situation so they achieve a sense of functioning just as well as ‘healthy’ families (Gannoni & Shute 2010; Huygen et al. 2000). The ability to maintain healthy family functioning, adapt to stressful life events and develop strengths and skills as a result, reflects a family’s resilience (Rolland & Walsh 2006).

A family resilience framework can guide mental health promotion interventions. Strategies for promoting wellbeing can target the processes and factors involved in coping, adjustment and resilience (Walsh 2002). Theoretical models of family resilience describe a dynamic process through which families are able to adjust in healthy ways to change, cope with stressors, build on strengths, draw on protective factors and modify family functioning to support optimal adaptation in the face of adverse experiences (Rolland & Walsh 2006; Walsh 2002; Benzies & Mychasiuk 2009; McCubbin & McCubbin 1996). Resilience-based mental health promotion interventions can assist families to identify their strengths, recognise the protective factors and resources they can utilise and build on within their family and the environment, and provide opportunities to practice specific strategies to improve coping and family functioning (Padesky & Mooney 2012).

Interventions aimed at improving the mental health and wellbeing of families living with childhood illness provide evidence that helping families to identify positive coping skills (Barrera et al. 2002; Sahler et al. 2013; Sansom-Daly et al. 2012; Scholten et al. 2013), enhance family functioning (Hocking & Lochman 2005; Jerram et al. 2005; Lobato & Kao 2002; Loding et al. 2008) and access resources including social support (Chernoff et al. 2002; Merkel & Wright 2012; Monaghan et al. 2011; Stewart et al. 2011) result in positive patient and family outcomes. There is evidence that interventions targeting parents have positive outcomes for the child and family, given that parental wellbeing and family functioning has a significant impact on the child’s health outcomes and coping with the illness (Sein 2001; Raina et al. 2005; Tong et al. 2008; Scholten et al. 2013; Hocking & Lochman 2005; Eccleston et al. 2012; Patterson & Geber 1991; Peek & Melnyk 2010) and sibling adjustment (Sahler et al. 2013; Drotar & Crawford 1985). The literature also suggests that the efficacy and acceptability of parent based interventions is enhanced when conducted in a group setting, as the group provides the additional benefit of opportunities for exchange of information, shared experience and mutual support for parents experiencing child-illness related stress (Chernoff et al. 2002; Merkel & Wright 2012; McCarthy & Sebaugh 2011; Turner et al. 2001).

Although existing research supports the efficacy of interventions to improve the mental health and wellbeing of families living with chronic illness, there are a number of limitations to the existing evidence. Published reviews report a focus on improving disease management (e.g. enhancing treatment adherence, reducing or managing symptoms) with fewer studies addressing psycho-social outcomes or using a health promotion approach (Peek & Melnyk 2010; Barlow & Ellard 2004; Glasscoe & Quittner 2008). Furthermore, previous studies have used insufficiently validated outcome measures, short follow up periods, small sample sizes, non-standardized intervention delivery or provided inadequate detail of intervention content (Eccleston et al. 2012; Barlow & Ellard 2004; Glasscoe & Quittner 2008; Pai et al. 2006). Previous interventions have also been limited by the absence of a theoretical framework for a project’s design and reliance on delivery by mental health professionals within clinical settings (Peek & Melnyk 2010; Marsac et al. 2012). Thus, there is a need for studies that develop and evaluate interventions designed to improve the mental health of families living with childhood chronic illness that address these limitations.

This paper describes the methodology for the Child Illness and Resilience program (CHiRP). The CHiRP program is a stepped-care mental health promotion intervention guided by family resilience theory designed to support families who care for a child or young person with chronic illness. The intervention resources will assist families to identify existing strengths and provide strategies that target key protective factors and processes that enhance family resilience, such as family functioning, coping skills and utilising resources including social support.

### Study aim and hypotheses

This study aims to improve the resilience and wellbeing of families caring for a child living with chronic illness. Specifically, the objectives of the study are to: 1) improve the capacity of health services to provide family resilience information and strategies to families; 2) determine if the CHiRP resources are acceptable to parents; 3) increase parents knowledge and confidence to implement strategies to improve their family resilience; 4) promote parental help seeking behaviours and 5) improve the resilience and psychological wellbeing of families by providing a stepped care intervention to parents that increases in intensity according to the family’s situation. It is hypothesised that a significant positive improvement in outcome measures of constructs indicating family resilience (parental wellbeing, family functioning, family beliefs, and perceived social support) will be observed between baseline and follow up assessments as a result of receiving a family resilience self-directed booklet. Furthermore, for parents who are experiencing psychological distress, it is hypothesised that participation in a parent information support group (in addition to receiving the booklet) will result in greater improvement on the same outcome measures. It is further anticipated that participants will report that the intervention content and delivery style is acceptable.

## Methods/Design

### Study design and setting

The setting is a paediatric hospital in regional New South Wales that provides healthcare services to approximately 16,675 children per year who reside in the Newcastle, Hunter and New England regions (Australia). The intervention uses a stepped care design, such that increasing levels of intervention support are provided to families living with childhood chronic illness based on the level of parental distress. Step one involves the routine dissemination of a Family Resilience and Wellbeing Fact Sheet using single group assignment. Step two involves the targeted dissemination of a parent-focussed Family Resilience and Wellbeing information and activity booklet and will employ a repeated measures pre-post design. Step three involves the active participation of parents in a Family Resilience and Wellbeing Information Support Group and will employ a randomised waitlist control design. The dissemination strategy and research design for each step of the intervention is outlined in Figure 1.

**Figure 1 Fig1:**
[figure not shown]
**Flow diagram of CHiRP research design.**

### Participants and recruitment

Note, throughout this study, “parents” are defined as the adults who identify as being the primary carer of the child attending the outpatient clinic (this could include the biological parent, guardian or other adult family member) and “child” refers to a person less than 18 years of age.

#### Step 1 routine dissemination: fact sheet intervention

All parents who have a child who is discharged from the paediatric hospital will receive a Family Resilience and Wellbeing Fact Sheet. This will be automatically printed with paediatric discharge summaries and routinely disseminated alongside normal clinical practice. This component of the intervention will ensure all families who have a child discharged from the wards of the paediatric hospital, regardless of the reason for admission, will receive standardised brief family resilience and wellbeing support information. There will be no direct data collection from this group.

#### Step 2 targeted dissemination: booklet intervention

All parents who have a child who attends one of four selected outpatient clinics at the paediatric hospital will be considered eligible to participate in this stage of the intervention. The outpatient clinics at the paediatric hospital were selected for inclusion based on patient occupancy, illness presentations and clinic attendance rates. The clinics include Cystic Fibrosis, Diabetes, Gastroenterology and Rheumatology. These clinics provide a service predominantly to children living with a diagnosed chronic illness. Clinics operate once a week on a rotating basis and provide appointments to approximately 350 children per month in total.

Parents with children attending these selected outpatient clinics will be invited to participate in the program via a mailed invitation that includes the participant information statement, consent form and questionnaire. This will be delivered a minimum of two weeks prior to their child’s clinic appointment. The booklet will be provided to participants once the research team receives the completed questionnaire.

#### Step 3 active dissemination: parent information support group intervention

Participants who report psychological distress at the 3-month follow up of Step 2 will be considered eligible to participate in Step 3 of the intervention. Psychological distress will be defined according to cut off scores on the Kessler Psychological Distress Scale (K10) (Kessler et al. 2003). There is some evidence that support groups are of optimal benefit for this portion of the target population (Turner et al. 2001). All parents reporting a K10 score above 15 (Slade et al. 2011) will be eligible for the group. Eligible parents will be contacted by phone by a member of the CHiRP research team and invited to attend an Information Support Group. Participants who agree to attend the Information Support Group will be randomly allocated to the group or waitlist condition using standard statistical computer software. Researchers will not be blinded to group assignment. Participants will be notified by phone and letter of the date of group commencement.

### Data collection procedures

#### Step 1 routine dissemination: fact sheet intervention

Routine collection of discharge data from the paediatric hospital over the intervention period (using the NSW Health Admitted Patient Data Collection) will provide an estimate of the number of families who have received the Fact Sheet.

#### Step 2 targeted dissemination: booklet intervention

As per Figure 1, baseline data for Step 2 will be collected through the CHiRP Parent Outpatient Survey. This will be completed by all participants who participate in Step 2, prior to receiving the Booklet intervention. The questionnaire will take approximately 20 minutes to complete and a random identification code will be generated to maintain participant confidentiality. Participants will complete the questionnaire at home or while waiting for the clinic appointment, and it will be available to complete in hard copy or online. Baseline data collection for Step 2 will occur from September 2013 to March 2014.

Follow up data will be collected from all participants in Step 2 at three and six months after completing the baseline assessment and receiving the Booklet intervention. On both follow up occasions, to minimise attrition, participants will receive a prompt letter advising that follow up will occur. Participants will be contacted by phone approximately two weeks after receiving the prompt letter and be given the option to complete the questionnaire over the phone with a member of the CHiRP team, be sent the questionnaire to complete in hard copy (and return it with a reply paid envelope), or complete the questionnaire online. Data collection for the three-month follow up assessment of Step 2 will occur between January – June 2014. Data collection for the 6-month follow up assessment is anticipated to occur between April - September 2014.

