#### Step 2 targeted dissemination: booklet intervention

Using oneway analyses of variance (ANOVA), the relationship between demographic data (e.g. gender, age categories, ethnicity, socioeconomic level, help-seeking behaviour categories) and baseline outcome measures will be explored.

The impact of the booklet intervention will be examined using analysis of covariance (ANCOVA) to compare changes in mean scores from baseline to three-month follow-up on the outcome measures for all participants in Step 2 (n ≈ 353). To test for sustained change, a second analysis of the Step 2 participants will use a repeated measures mixed model to compare mean scores on outcome measures at baseline, three and six month follow-up for the participants who did *not* move into Step 3 (the Information Support Group Intervention phase). Further analyses will adjust for baseline characteristics to control for any confounding effects.

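### Step 2 adds a phone-interview option only after baseline, so in an uncontrolled pre-post comparison any mode effect among parents who switch is counted in the booklet estimate

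*Protocol article*

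**What the plan says.** **Baseline mode.** The protocol article, Data collection procedures, Step 2, has parents fill in the baseline questionnaire "at home or while waiting for the clinic appointment, and it will be available to complete in hard copy or online". No phone option is listed.

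**Follow-up mode.** The same section says that at three and six months parents get a prompt letter and then a call, at which they will "be given the option to complete the questionnaire over the phone with a member of the CHiRP team", be mailed a paper copy, or answer online. The letter-and-call procedure is introduced as a way to limit attrition.

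**Design and analysis.** Under Study design and setting, Step 2 "will employ a repeated measures pre-post design". Under Statistical analyses, Step 2, the main analysis will "compare changes in mean scores from baseline to three-month follow-up on the outcome measures for all participants in Step 2", with n of about 353. On adjustment, the section says: "Further analyses will adjust for baseline characteristics to control for any confounding effects".

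**Gate to Step 3.** Under Participants and recruitment, Step 3: "Participants who report psychological distress at the 3-month follow up of Step 2 will be considered eligible" for Step 3. The threshold is set by "All parents reporting a K10 score above 15". The three-month data also serve as the Step 3 baseline (Data collection procedures, Step 3).

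**The concern.** The outcomes are self-reports of distress, family functioning, perceived support and family beliefs. Speaking the answers to a member of the study team is a different measurement condition from writing them down alone, and it becomes available only after the booklet has been given. In a controlled comparison with the same options in both arms, a mode effect would largely cancel. Step 2 has no second arm, so the baseline-to-follow-up change is itself the estimate of the booklet's effect. A variable that first arises at follow-up cannot be removed by adjusting for baseline characteristics.

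Two things are at stake. The first is whether a Step 2 change can be read as a response to the booklet rather than, in part, to a different way of asking. The second is the K10 gate: the three-month score is the first that may come by phone, so whether a parent near the threshold qualifies may depend on how the questionnaire was answered.

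**Working it through.** **Inputs from the protocol article.** Hypothesised Step 2 effect 0.2, alpha 0.05, power 0.8 and minimum n of 98 (Sample size); analysis n of about 353 (Statistical analyses, Step 2); about 120 parents in Step 3 (Sample size).

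**Inputs assumed, because the documents do not give them.** Phone share *p* from 0.3 to 0.7; mode shift *m* from 0.1 to 0.3 baseline SD, in either direction; pre-post correlation ρ of 0.5, which makes the SD of change equal to the baseline SD, since √(2(1 − ρ)) = 1. Sidedness of the test is not stated; two-sided is used.

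**The plan's own figure.** A plain one-sample calculation gives n = ((1.96 + 0.842)/0.2)² ≈ 197, not 98. The stated 98 appears if 0.2 is in baseline-SD units and ρ = 0.75: 2 × (1 − 0.75) × 196.2 = 98.1. That is a separate matter. It is used here only as a reason to show ρ = 0.75 as a sensitivity case.

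**Step 1: distortion of the mean change.** Only switchers contribute, so distortion = *p* × *m*.
- Low: 0.3 × 0.1 = 0.03 SD (15% of 0.2)
- Middle: 0.5 × 0.2 = 0.10 SD (50%)
- High: 0.7 × 0.3 = 0.21 SD (105%)

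**Step 2: chance of a significant change if the booklet does nothing and the shift is favourable.** With λ = distortion × √n / √(2(1 − ρ)), the probability is Φ(λ − 1.96) + Φ(−λ − 1.96). At n = 353, √n = 18.79.

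| Distortion | λ (n = 353, ρ = 0.5) | n = 353, ρ = 0.5 | n = 353, ρ = 0.75 | n = 98, ρ = 0.5 | n = 98, ρ = 0.75 |
|---|---|---|---|---|---|
| 0.03 SD | 0.56 | 9% | 13% | 6% | 7% |
| 0.10 SD | 1.88 | 47% | 76% | 17% | 29% |
| 0.21 SD | 3.95 | 98% | >99% | 55% | 84% |

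The nominal rate is 5%. If the shift is unfavourable, the same distortions are subtracted from any true effect: a true 0.2 would be seen as 0.17, 0.10 or −0.01 SD.

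**Step 3: the gate.** For illustration, suppose 120/353 = 34% would exceed 15 if all self-completed, on a normal latent score (threshold at 0.412 SD). If the phone lowers reported distress by *m*, the crossing rate among phone users is 1 − Φ(0.412 + *m*): 30.4%, 27.0% and 23.8% for *m* = 0.1, 0.2 and 0.3. The number affected is 353 × *p* × (0.34 − that rate):
- Low: 353 × 0.3 × (0.340 − 0.304) ≈ 4 fewer eligible
- Middle: 353 × 0.5 × (0.340 − 0.270) ≈ 12 fewer
- High: 353 × 0.7 × (0.340 − 0.238) ≈ 25 fewer

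If the phone raises reported distress, the crossing rates become 37.7%, 41.6% and 45.5%, and about 4, 13 and 28 more parents qualify.

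**The case against.** - **Direction is unknown.** A reader might infer that answers given to an interviewer will look better, so that the phone option manufactures improvement and screens distressed parents out of Step 3. Nothing in the documents supports a direction. This objection stands: the point is confounding of unknown sign, and the false-positive rates are conditional on a favourable shift.
- **The size may be trivial.** At the low end the error rate is 9%, or 6% at the stated minimum sample, against 5%. This stands, and is why the whole range is shown.
- **The phone is optional.** Two of the three follow-up modes are self-completed, and no default is named. It would be wrong to describe the three-month K10 as phone-collected or to read a preference into the order of the list. This stands: only switchers contribute.
- **Step 3 is randomised after the gate.** A reader might infer bias in the group-versus-waitlist comparison from the gate. That does not follow; a mode shift at the gate changes who enters and their baseline values, not the comparability of the arms.
- **Acceptability, knowledge and confidence** might seem affected in the same way. They are described only for the follow-up survey, so no baseline-to-follow-up change of mode is described for them.
- **Retention matters.** Selective loss is also a bias in an uncontrolled study, and the follow-up contact serves that aim. This stands as a reason not to withdraw the phone option or hold it back for non-responders.
- **The uncontrolled design is the larger weakness.** True; a consistent mode would not make the change attributable to the booklet. The Discussion concedes limited generalisability for this design but does not address the mode difference, which is an avoidable addition to the problem.
- **Mode handling may sit in a fuller document.** It may. The asymmetry itself is fixed in the article, however, and since the phone is absent at baseline, no covariate can fully separate time from mode in switchers.

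**Conclusion.** The concern holds as structural confounding. Phone completion exists only after baseline, Step 2 has no control group, and the named adjustment cannot reach a follow-up variable, so any mode effect among switchers enters the Step 2 change. Under the assumed ranges the distortion runs from 0.03 to 0.21 SD in either direction, that is, from minor to as large as the hypothesised 0.2. If the shift is favourable, the booklet inert, n about 353 and the SD of change equal to the baseline SD, a significant result would occur about 9%, 47% and 98% of the time at 0.03, 0.10 and 0.21 SD. These amounts rest on assumed phone shares and shifts; the documents establish only the asymmetry. The effect on the gate is a change in eligibility of uncertain sign, with no claim against the randomised Step 3 contrast.

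**What to change.** 1. At the three- and six-month calls, encourage completion in the parent's baseline mode (paper or online), and keep the phone option available to protect retention.
2. Record the mode of completion at every wave.
3. Pre-specify a sensitivity analysis reporting the Step 2 change in parents who self-completed at both waves, beside the result for all participants.
4. State that the change will not be attributed to the booklet if the two results differ materially.

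The cost is one extra variable, one extra analysis and a small change to the call wording. The both-waves subset is self-selected and somewhat smaller, so agreement between the two results is reassuring rather than conclusive, and a difference may reflect selection as well as mode. A mode covariate alone would not be enough.
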